#### Inclusion and Exclusion Criteria

All adults aged 18 years and older, with a confirmed diagnosis of hypertension and diabetes, residing within the targeted health facility’s catchment area, and capable of providing written informed consent will be eligible for enrollment.

Exclusion criteria will include the following: (1) individuals having hypertension- and diabetes-related complications that cannot be managed in a primary care setting, (2) individuals who are pregnant or planning to become pregnant during the course of the trial, (3) individuals who will not be able to stay within the catchment area of the clinic where they are enrolled for the duration of the trial, and (4) individuals who will not be able to give consent for any reason, such as severe mental health disorders.

#### Recruitment of Participants

Participants will be recruited by trained research assistants every day of the 1-week recruitment period. The recruitment process will be done concurrently at control and intervention sites. Baseline data will be collected on the day of the recruitment, and research assistants will not be aware of group allocations during the recruitment and the baseline data collection periods.

#### Outcome Measures

The outcome evaluation for this study will be based on data collected both at baseline and during the postintervention follow-up (after 6 months). Data collection tools will be identical for data collection at both periods and include information on patient’s demographics, disease history, lifestyle behaviors, medication use, primary use of health care services, and hospitalizations. Height, weight, waist circumference, glycosylated blood glucose levels, and blood pressure will also be measured.

The primary study outcomes will be blood pressure and blood glucose levels as well as levels of adherence to recommended lifestyle modifications. Other outcomes will include changes in medication adherence and additional health-related outcomes, such as frequency of hospitalization or the occurrence of complications.

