**Methods:**

This is a 6-month–long cluster randomized controlled trial, which will be conducted in primary health care clinics in the city of Harare. A total of 14 clinics will be randomly allocated into either the intervention or control group. A total of 680 (49 participants per clinic) adult patients with hypertension and diabetes will be enrolled for the trial. Participants in the intervention arm will receive a simple health literacy intervention on lifestyle modification, which will be delivered by trained CHWs, while those in the control arm will receive usual care. The intervention consists of 4 face-to-face interactive educational sessions and monthly support visits by trained CHWs and will be carried out over a period of 6 months. The primary study outcomes will be blood pressure and blood glucose levels and levels of adherence to the recommended lifestyle modifications. Other outcomes will include adherence to medication. Data management and analysis will be done using Epi Info software, and the data will be analyzed using the intention-to-treat principle.

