##### Lifestyle Modifications

Patients’ levels of adherence to recommended lifestyle modifications will be assessed using self-reported questions adapted from the Hypertension Self-Care Activity Level Effects Scale (H-SCALE) questionnaire. The H-SCALE is a validated self-reported questionnaire for assessing self-care practices for hypertension prevention and control [26]. The questionnaire assesses 5 key recommended lifestyle modifications (ie, low-salt diet, physical activity, smoking cessation, weight management, and abstinence from alcohol) as well as adherence to medication. Table 2 shows how each recommended lifestyle modification will be assessed based on the H-SCALE.

**Table 2 table2:** Assessment of lifestyle modifications using an interviewer-administered questionnaire adapted from the Hypertension Self-Care Activity Level Effects Scale (H-SCALE).

Recommended lifestyle modification	The WHO^a^ recommendation	Assessment method
Weight reduction and management	Maintain normal body weight (BMI 18.5-24.9 kg/m^2^)	First, the patient’s BMI will be assessed based on the patient’s height and weight. All patients with a BMI above 24.9 will be considered as overweight. Second, 10 questions will be used to assess activities undertaken to manage weight through dietary practices, such as reducing portion size, making food substitutions, and exercising to lose weight. Participants who say yes to 5 or more questions will be nonadherent to recommended weight management practices.
Reducing dietary salt intake	Reduce dietary salt intake to less than 2400 mg of sodium per day or less than 6000 mg sodium chloride per day.	A total of 6 questions will be used to assess practices related avoiding salt while cooking and avoiding foods high in salt content. Patients who answer yes to 3 or more questions will be considered as nonadherent to a low salt diet.
Reducing dietary fat intake	Avoid foods high in cholesterol and fat content	A total of 2 questions will be used to assess practices related to avoiding foods high in cholesterol and fat content. Patients who answer yes to any 1 question will be considered as nonadherent to a low fat or cholesterol diet.

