##### Hypertension and Diabetes Control

Patient’s hypertension and diabetes control will be assessed by blood pressure and HbA_1c_ measurements, respectively*.* Blood pressure of 140/90 mm Hg or higher will be considered uncontrolled hypertension, while an HbA_1c_ level above 8% (53 mmol/mol) will be considered uncontrolled diabetes [27].

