#### Data Analysis

Data analysis will be performed using the Epi Info (Centers for Disease Control and Prevention) software. The primary analysis will be conducted under the intention-to-treat principle. For individual outcomes, proportions will be compared using the chi-square test, and continuous measures will be compared using 2-tailed *t* tests. Stratified analysis will be conducted to control for confounding and assess the effect modification by demographic variables and medication adherence. The effects of the intervention will be tested by ANOVA, which will allow adjustment for baseline differences between groups. Two-sided *P* values and 95% CIs will be used to determine statistical significance of results.

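### Three unranked primary domains, each judged by its own 95% interval with no stated success rule, leave the chance of a false-positive primary result at about 11–14%, and higher if components are tested separately

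*Protocol article*

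**What the plan says.** Outcome Measures gives the primary set as "The primary study outcomes will be blood pressure and blood glucose levels as well as levels of adherence to recommended lifestyle modifications". The abstract's Methods paragraph gives the same three domains: "The primary study outcomes will be blood pressure and blood glucose levels and levels of adherence to the recommended lifestyle modifications". Neither place ranks them or says what pattern of results would count as success.

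The domains are broader than single variables:

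- **Blood pressure and glucose.** The section on hypertension and diabetes control says: "Patient’s hypertension and diabetes control will be assessed by blood pressure and HbA_1c_ measurements, respectively". It adds cut-offs, for example "Blood pressure of 140/90 mm Hg or higher will be considered uncontrolled hypertension". It does not say whether the resulting proportions are primary tests.
- **Lifestyle.** The text says "The questionnaire assesses 5 key recommended lifestyle modifications", and then "Table 2 shows how each recommended lifestyle modification will be assessed based on the H-SCALE". Table 2 has seven rows: weight, salt, fat, fruit and vegetables, smoking, alcohol and physical activity. Each row has its own rule for adherent or nonadherent. No overall lifestyle score is defined.

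Data Analysis assigns chi-square tests to proportions and t tests to continuous measures, adds an ANOVA adjusting for baseline, and closes with the decision rule: "Two-sided *P* values and 95% CIs will be used to determine statistical significance of results". A 5% level is implied by the 95% interval but is not written out. The Sample Size section gives one set of inputs (80% power, effect size 0.5, SD 1) and ties it to no named outcome, so it does not reveal an intended lead endpoint.

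**The concern.** When several outcomes share primary status and each is judged alone at 5%, the chance that at least one is significant by accident exceeds 5%. With no success rule, a reader of the eventual report cannot tell whether one significant primary result among three is the outcome the trial was designed to detect or one of several chances to find something.

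This matters here because the domains differ in kind. Lifestyle adherence is self-reported and can be split into the most components. The Strengths and Limitations section regards the physiological measures as more objective, but the primary set gives them no priority. A significant result on one behaviour, with null pressure and HbA1c, could be reported as success on a primary outcome without departing from the text.

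**Working it through.** **Plan's own figure.** The article states no familywise error rate, so there is none to reproduce. The check uses the primary set (Outcome Measures), the behaviours (Lifestyle Modifications and Table 2) and the per-result rule (Data Analysis).

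**Step 1: count the tests.**
- Narrow reading, one test per domain: 3.
- Upper case, every component tested: systolic, diastolic and HbA1c (3), plus 5 behaviours from the text or 7 from Table 2. That is 3 + 5 = 8 or 3 + 7 = 10.

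The upper case is an assumption. No section says that each component is a separate primary test.

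**Step 2: familywise error if any one result counts, independent tests at 5%.** The formula is 1 − 0.95^k.
- k = 3: 1 − 0.95³ = 14.3%
- k = 8: 1 − 0.95⁸ = 33.7%
- k = 10: 1 − 0.95¹⁰ = 40.1%

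**Step 3: allow for correlation.** The article gives no correlations, so a range was assumed. Equally correlated normal test statistics were simulated with 200,000 replicates per setting (the column for correlation 0 uses the exact values from step 2).

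| Tests | 0 | 0.3 | 0.5 | 0.7 |
|---|---|---|---|---|
| 3 | 14.3% | 13.7% | 12.6% | 11.0% |
| 10 | 40.1% | 35.2% | 28.7% | 21.3% |

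**Step 4: count only false results that favour the intervention.** Each test then has a 2.5% chance. For independent tests, 1 − 0.975³ = 7.3% and 1 − 0.975¹⁰ = 22.4%. At correlation 0.7 the simulated values are 5.5% and 10.6%. The comparison figure for a single test is 2.5%.

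**Step 5: cost of control.** Holm's first step for three tests is 0.05/3 = 0.0167. A comparison with 80% power at two-sided 0.05 has an expected test statistic of 1.960 + 0.842 = 2.802. The critical value at 0.0167 is 2.394, so power is Φ(2.802 − 2.394) = Φ(0.408), about 66%.

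In sample size terms, with effect 0.5 and SD 1, n per arm before any allowance for clustering is 2(z_α/2 + z_power)²/0.5²:
- at 0.05: 8 × 2.802² = 62.8, so 63
- at 0.0167: 8 × (2.394 + 0.842)² = 83.8, so 84

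**The case against.** The best defence is that this is a condensed article. Hierarchy and multiplicity adjustment often sit in an analysis plan, and that plan is not shown. Their absence alone would not be a finding. The point therefore rests on what the article does state: several primaries without ranking, and a rule that decides significance result by result. A later plan could add a hierarchy, but it would have to narrow the published primary definition.

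A second defence is that the Introduction words the hypothesis jointly across lifestyle adherence, medication adherence, and glucose and pressure. If success required all primaries, no adjustment would be needed. That is correct, but the article never says so, and the percentages above are conditional on an any-one rule.

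Three stronger readings are tempting and not supported:

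- **That a false primary success is likely.** Every figure above is below even odds. Independent tests would have to number 14 before the chance passed 50% (1 − 0.95¹⁴ = 51.2%).
- **That about ten endpoints are each formally tested at P<.05.** The article lists lifestyle adherence as one domain, the count is 8 or 10 depending on text or table, and the threshold is only implied. A single overall adherence measure is not defined, but it is not excluded either. The control cut-offs are not declared primary.
- **That the winning outcome would be picked after seeing the data.** Nothing in the article says this. It only leaves the possibility open.

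Self-report bias in an unblinded trial and tests that ignore clustering are separate matters. Multiplicity control repairs neither.

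**Conclusion.** The point holds in a limited form. As written, the plan has three equal primary domains, a per-result significance rule and no success rule. If any one domain suffices and each is tested once, the familywise error is 14.3% when independent and about 11–14% for correlations up to 0.7, which is two to three times the nominal 5%. The figures of 34–40% (independent, 8 to 10 tests) and 21–35% (ten tests, correlations 0.7 to 0.3) apply only if components are tested separately. The correlations and the any-one rule are assumptions, and each test is taken to have a true 5% level. The gap should be closed before analysis. It does not undermine the trial's design.

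**What to change.** Before follow-up data are examined:

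1. Name one measure per domain, for example 6-month systolic pressure, 6-month HbA1c and one summary lifestyle adherence score.
2. State the success rule. Either test the three with Holm at two-sided 0.05 (thresholds 0.0167, 0.025, 0.05 from smallest to largest P value, stopping at the first failure), which is valid under any correlation, or declare that all three must succeed, which needs no adjustment.
3. Make the control proportions and the single behaviours secondary.
4. Before building the score, reconcile Table 2. A yes to 5 or more weight-management activities is classed as nonadherent, and the salt row, about avoiding salt, appears to run the same way. The fat row is worded similarly, whereas fruit and vegetables and physical activity score yes as adherent. Summing these rows without checking the item wording in Multimedia Appendix 1 could combine items scored in opposite directions. The count of 5 or 7 behaviours must also be settled.

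**Cost.** No new data are needed, but step 4 is more than a wording change. Under Holm, power at the strictest step falls from 80% to about 66%. Recruitment is reported as complete, so added participants cannot recover it. The all-must-succeed rule has its own cost: with 80% power for each of three independent outcomes, the chance that all succeed is 0.80³ = 51%, and more if they are positively correlated.

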#### Assessment of Primary and Secondary Outcomes

A consolidated interviewer-administered questioner comprising of all measures (as detailed in Multimedia Appendix 1) will be used to collect data. The interviewer-administered questionnaire consists of 5 sections, as follows: section A (sociodemographic characteristics), section B (details of the patient’s condition), section C (blood pressure, BMI, and glycosylated hemoglobin [HBA_1c_] measurements), section D (adherence to lifestyle modifications), and section E (adherence to medication).

##### Lifestyle Modifications

Patients’ levels of adherence to recommended lifestyle modifications will be assessed using self-reported questions adapted from the Hypertension Self-Care Activity Level Effects Scale (H-SCALE) questionnaire. The H-SCALE is a validated self-reported questionnaire for assessing self-care practices for hypertension prevention and control [26]. The questionnaire assesses 5 key recommended lifestyle modifications (ie, low-salt diet, physical activity, smoking cessation, weight management, and abstinence from alcohol) as well as adherence to medication. Table 2 shows how each recommended lifestyle modification will be assessed based on the H-SCALE.

**Table 2 table2:** Assessment of lifestyle modifications using an interviewer-administered questionnaire adapted from the Hypertension Self-Care Activity Level Effects Scale (H-SCALE).

Recommended lifestyle modification	The WHO^a^ recommendation	Assessment method
Weight reduction and management	Maintain normal body weight (BMI 18.5-24.9 kg/m^2^)	First, the patient’s BMI will be assessed based on the patient’s height and weight. All patients with a BMI above 24.9 will be considered as overweight. Second, 10 questions will be used to assess activities undertaken to manage weight through dietary practices, such as reducing portion size, making food substitutions, and exercising to lose weight. Participants who say yes to 5 or more questions will be nonadherent to recommended weight management practices.
Reducing dietary salt intake	Reduce dietary salt intake to less than 2400 mg of sodium per day or less than 6000 mg sodium chloride per day.	A total of 6 questions will be used to assess practices related avoiding salt while cooking and avoiding foods high in salt content. Patients who answer yes to 3 or more questions will be considered as nonadherent to a low salt diet.
Reducing dietary fat intake	Avoid foods high in cholesterol and fat content	A total of 2 questions will be used to assess practices related to avoiding foods high in cholesterol and fat content. Patients who answer yes to any 1 question will be considered as nonadherent to a low fat or cholesterol diet.
Increasing fruit and vegetable consumption	Consume 5 servings (equivalent of 5 tablespoons) of vegetables and 3 servings (equivalent of to at least 3 fruits) of fruits every day.	A total of 2 questions will be asked to assess adherence to fruits and vegetables. Patients who answer yes to any 1 question will be considered as adherent to a high fruit and vegetable diet.
Smoking	Avoid smoking	Smoking status will be assessed by 1 question. All patients who answer yes to the question will be considered nonadherent to nonsmoking recommendations
Moderation in alcohol consumption	Limit alcohol consumption to no more than 2 drinks (eg, 24 oz of beer, 10 oz of wine, or 3 oz of 80-proof whiskey) per day in men and no more than 1 drink per day in women and lighter-weight persons.	Alcohol intake will be assessed using 2 questions. Participants who answer yes to any 1 of the questions will be considered nonadherent to the alcohol recommendation moderation.
Physical activity	Engage in regular aerobic exercises, such as brisk walking for at least 30 minutes per day, for at least 5 days a week.	Physical activity will be assessed by 1 question. Participants who answer yes to the question will be considered as being adherent to the physical activity recommendation.

^a^WHO: World Health Organization.

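### The weight management row of Table 2 scores recommended activities as nonadherence, so that component of a primary outcome is reported with the wrong sign; salt and fat need a polarity check

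*Protocol article*

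**What the plan says.** The article's Outcome Measures section states: "The primary study outcomes will be blood pressure and blood glucose levels as well as levels of adherence to recommended lifestyle modifications". The Lifestyle Modifications section refers to Table 2 for the assessment of each recommendation.

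- **Weight.** After a BMI step, the row says "10 questions will be used to assess activities undertaken to manage weight through dietary practices, such as reducing portion size, making food substitutions", and adds exercising to lose weight as a third example. The rule is "Participants who say yes to 5 or more questions will be nonadherent to recommended weight management practices".
- **Salt.** "A total of 6 questions will be used to assess practices related avoiding salt while cooking and avoiding foods high in salt content". The rule is "Patients who answer yes to 3 or more questions will be considered as nonadherent to a low salt diet".
- **Fat.** Two questions are described as covering practices of avoiding fatty and high-cholesterol foods. The rule is "Patients who answer yes to any 1 question will be considered as nonadherent to a low fat or cholesterol diet".
- **Fruit and vegetables.** There are two questions, and the rule is "Patients who answer yes to any 1 question will be considered as adherent to a high fruit and vegetable diet".
- **Physical activity.** One question; yes counts as adherent.
- **Smoking and alcohol.** One and two questions respectively; any yes counts as nonadherent.

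The article says that the questionnaire itself is in Multimedia Appendix 1, which is not among the documents at hand. The text shown mentions no reverse coding.

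**The concern.** In the weight row, what the items measure and what the rule does with them point in opposite directions. Every activity the row names is one that a patient following the advice would report. The rule nevertheless classes patients who report many of them as nonadherent.

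Lifestyle adherence is the first objective in the abstract and the first hypothesised effect in the Introduction. If the intervention works and patients take up more of these activities, an analyst applying Table 2 as printed would report that it lowered adherence to weight management. If the key is instead corrected silently after the results by arm are known, that would look like a post hoc change to a primary outcome.

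**Working it through.** The plan states no figure to reproduce here. The check is to compare each row's item description with its rule, and then to see what a reversed rule does to a comparison between arms.

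**Step 1: direction, row by row (all from Table 2)**

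| Row | Items, as described | A yes pattern means | Direction |
|---|---|---|---|
| Weight | 10 on helpful activities | 5 or more: nonadherent | Contradictory |
| Salt | 6 on avoiding salt | 3 or more: nonadherent | Conflicts as described; depends on item wording |
| Fat | 2 on avoiding fat and cholesterol | Any 1: nonadherent | Conflicts as described; depends on item wording |
| Fruit and vegetables | 2 on consumption | Any 1: adherent | Coherent |
| Smoking | 1 on smoking status | Yes: nonadherent | Coherent if it asks about smoking |
| Alcohol | 2 on intake | Any 1: nonadherent | Coherent if they ask about drinking above the limit |
| Physical activity | 1 | Yes: adherent | Coherent |

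The table therefore has no general convention that yes means nonadherent. Fruit and vegetables and physical activity both score yes as adherent.

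**Step 2: effect on the comparison**

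Let p_C and p_I be the proportions in the control and intervention arms that reach the yes cut-off. If reaching it means adherent, the difference is d = p_I - p_C. Under the reversed rule the adherent proportions are 1 - p_C and 1 - p_I, and the difference is (1 - p_I) - (1 - p_C) = -d. This holds for any rates.

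**Step 3: illustrative size**

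The documents give no item-level rates. Assume a common probability of yes per item and independent items, so that the proportion reaching the cut-off is a binomial upper tail. For weight, with 0.4 in the control arm and 0.5 in the intervention arm:

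- P(X ≥ 5; n = 10, 0.4) = 0.367 and P(X ≥ 5; n = 10, 0.5) = 0.623.
- If yes counts as adherent: 62.3% - 36.7% = +25.6 points.
- As written: 37.7% - 63.3% = -25.6 points.

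Over three assumed pairs (control, intervention):

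| Row and cut-off | 0.4, 0.5 | 0.4, 0.6 | 0.3, 0.5 |
|---|---|---|---|
| Weight, ≥5 of 10 | ±25.6 | ±46.7 | ±47.3 |
| Salt, ≥3 of 6 | ±20.1 | ±36.5 | ±40.1 |
| Fat, ≥1 of 2 | ±11.0 | ±20.0 | ±24.0 |

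Entries are percentage points: plus if yes counts as adherent, minus under the printed rule. The salt and fat lines apply only if a yes means that the avoiding practice is done.

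**The case against.** The strongest reply is that most of Table 2 cannot be judged without the appendix. Saying that questions concern avoiding salt names a topic, not what a yes means. Items asking whether salt is added would make the salt rule right and only its description loose. For fat, one yes out of two is a natural cut-off for unfavourable items, where a single lapse is enough, and the alcohol row uses the same form. This stands. A reader might infer that three of the seven rows are reversed, but the documents establish one.

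A reader might also infer that the primary outcome as a whole changes sign. The documents do not support that. They define no overall adherence score, blood pressure and blood glucose are primary outcomes too and are untouched, and BMI is assessed separately.

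It can further be said that the weight rule is a one-word slip in the article and that the data are scored correctly. That cannot be excluded, but nothing in the article corrects the rule, and the printed rule is the public reference. The appendix could rescue the weight row only if its items asked about the opposite of the activities the row names.

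Two neighbouring points are weaker. Calling the one-of-two fruit and vegetable rule too lenient assumes one question per food group. The text's mention of alcohol abstinence may describe the source scale, while the table's moderation target is the trial's own rule. Neither is a reversal.

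**Conclusion.** The weight management row contradicts itself. Applied as printed, it reverses the sign of the between-arm difference on that component of the lifestyle adherence primary outcome. This conclusion rests only on the row's own description of its items and needs no assumed rate.

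The salt and fat rows conflict with their descriptions in the same way, but a true reversal there is conditional on item wording that is not shown. The demonstrated effect is therefore one component of seven, with two more possible. The percentage-point figures are illustrations under assumed yes-probabilities and independent items, and should not be read as expected effects. Any consequence for a combined adherence measure is not computable.

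**What to change.** Before follow-up data are scored:

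1. **Weight.** Confirm the item wording in Multimedia Appendix 1, then correct the row so that yes to 5 or more means adherent.
2. **Salt and fat.** Check what a yes means for each item. Correct the rule if the items ask about avoidance, or the description if they ask about the unfavourable behaviour, so that the scoring direction matches the items.
3. **Record.** Issue the correction as a dated change to the scoring key and carry it into the analysis code.
4. **Minor.** Check whether one yes out of two matches the fruit and vegetable row's two-part recommendation, and reconcile abstinence in the text with moderation in the table for alcohol.

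The cost is one corrected row, a polarity check of eight items (six salt, two fat), and two wording checks. The change is to scoring and description only and needs no new data.

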##### Sample Size

Based on the recommendations for sample size calculation for cluster randomized controlled trials with a fixed number of clusters [32], a total of 680 participants will be required for the trial. Therefore, the study will comprise 14 clusters, with 49 participants per cluster. The sample size was calculated using the following parameters, obtained from the review of literature: 80% study power, 0.5 effect size, 1 SD, 0.05 coefficient of variation, and 20% lost to follow-up adjustment.

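### The 10-question weight-management and 6-question salt counts, parts of a primary outcome, are each cut to adherent or nonadherent, which discards graded information already collected; the power cost depends on inputs the article does not give.

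*Protocol article*

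**What the plan says.** Outcome Measures sets the primary outcomes: "The primary study outcomes will be blood pressure and blood glucose levels as well as levels of adherence to recommended lifestyle modifications".

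Table 2, under Lifestyle Modifications, then defines each component. For weight, "10 questions will be used to assess activities undertaken to manage weight through dietary practices", and the rule is: "Participants who say yes to 5 or more questions will be nonadherent to recommended weight management practices". For salt, "A total of 6 questions will be used to assess practices related avoiding salt while cooking and avoiding foods high in salt content", and the rule is: "Patients who answer yes to 3 or more questions will be considered as nonadherent to a low salt diet". Apart from BMI in the weight row, the only variable that Table 2 derives from either set of questions is a two-category one. It defines no total score, mean or graded level.

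Data Analysis gives the tests by type of variable: "proportions will be compared using the chi-square test, and continuous measures will be compared using 2-tailed" t tests. It adds an ANOVA for intervention effects with adjustment for baseline differences. It does not assign a test to each lifestyle component.

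Sample Size lists its inputs as "80% study power, 0.5 effect size, 1 SD, 0.05 coefficient of variation, and 20% lost to follow-up adjustment".

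**The concern.** A yes/no cut keeps only which side of the line a patient is on. With the salt cut at 3, a patient who goes from 0 to 2 yes answers, or from 3 to 6, shows no change. With the weight cut at 5, a move from 5 to 9 shows no change. A one-answer move from 2 to 3 (salt) or from 4 to 5 (weight) flips the category completely.

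Two features make this worth raising:

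- Self-reported practices are what a health literacy intervention acts on most directly. A graded behavioural gain is more likely to be missed on a cut count than on the count itself.
- The sample size rests on a standardised difference (0.5 with SD 1), which belongs to a quantitative measure. No adherence proportion appears anywhere in the article, so the stated 80% power does not describe a comparison of percent adherent.

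**Working it through.** **Inputs from the article.** 7 clinics per arm (Study Setting). 49 participants per clinic less 20% loss: 49 × 0.8 = 39.2, taken as 39 (Sample Size). Effect 0.5, SD 1, coefficient of variation 0.05 (Sample Size). Two-sided 5% level, implied by the 95% CIs (Data Analysis).

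**Not given.** An ICC, the score distribution, a control-arm adherence rate, and the expected effect on these items. These are assumed below and varied.

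**Step 1: can the ICC be recovered from the plan's own figure?** Without clustering, n = 2(1.96 + 0.84)² / 0.5² = 62.8, so 63 per arm. With k = 7 clinics per arm, the number per clinic is m = n(1 − ICC) / (k − n·ICC). With 0.05 read as an ICC, m = 63 × 0.95 / (7 − 3.15) = 15.5, so 16. The total is 14 × 16 = 224, or 224 / 0.8 = 280 after loss. The article states 680. Reaching 39 analysed per clinic needs 63(1 − ICC) = 39(7 − 63·ICC), so ICC = 210 / 2394 = 0.088. A coefficient-of-variation formula gives about 661 to 665, but only if an unstated control mean of about 5 SD is supplied. The stated inputs therefore do not fix the clustering, and a range is needed.

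**Step 2: analytic check, SMD 0.5, ICC 0.05.** Full scale: ncp = 0.5 / √(2(1 + 38 × 0.05) / 273) = 0.5 / 0.1458 = 3.43. On a noncentral t with 12 df, power is 88.2%.

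Now cut the same normal measure at the control mean. The proportions are 0.50 and 0.309, a difference of 0.191. The binary ICC, derived from the latent 0.05, is about 0.032 and 0.029 in the two arms. The variance is [0.25(1 + 38 × 0.032) + 0.213(1 + 38 × 0.029)] / 273 ≈ 0.0037, so ncp ≈ 3.16 and power is about 82.6%. The loss is 5.6 points. With the cut 0.5 SD from the control mean (31% of controls nonadherent), power is about 77.6%, a loss of 10.6. With only 16% of controls nonadherent, the loss is 22 points.

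**Step 3: item-level simulation.** Scores of 10 and 6 yes/no items in 14 clinics of 39, with a t test on clinic means of the score against a t test on clinic proportions. At SMD 0.5 and ICC about 0.05, two sets of runs with different item assumptions gave:

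| Run | Count power | Cut power | Loss, weight | Loss, salt |
|---|---|---|---|---|
| A (item endorsement 0.2–0.6) | 86–90% | 77–82% weight, 79–83% salt | 6–12 points | 4–11 points |
| B (item yes-rate 0.3–0.7) | 86–94% | 75–89% | 4.3–11.3 points | 5.0–8.3 points |

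Together: about 4 to 12 points.

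**Step 4: other admissible inputs (run B, both scores, loss in points).**

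| ICC | SMD 0.5 | SMD 0.3 |
|---|---|---|
| 0.0025 | 0.6–4.0 | 13–23 |
| 0.02 | 2.7–7.2 | 10–19 |
| 0.05 | 4.3–11.3 | 5–11 |
| 0.09 | 4.5–8.9 | 1–5 |

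The loss is small where power is near 100% on either scale, or low on both. It is largest in between. Monte Carlo error is about 1 point in run B. In every case computed the cut had lower power than the count.

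**Step 5: direction of the items.** Table 2 describes the salt questions as practices of avoiding salt, and the weight questions as things done to manage weight. Yet it codes many yes answers as nonadherent. In the same table, yes to fruit and vegetables or to physical activity is coded adherent. Reversing a scale does not change the information that a cut discards, but the sign of a score, and of the percentage, depends on settling this.

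**The case against.** The strongest reply has five parts.

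1. *No single loss figure is in the document.* This stands. The article calls 0.05 a coefficient of variation and does not tie the 0.5 to lifestyle items. A reader might infer a fixed loss of, say, 5 to 12 points; the documents do not support that.

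2. *At SMD 0.5 the cut still leaves roughly the planned power.* This largely stands. At ICC 0.05 the simulated cut power is 75 to 89%, around the stated 80%, and with little clustering it stays at 96% or more. A reader might infer that the cut leaves the trial underpowered; that does not follow at the stated effect. The cost bites if the true effect is smaller.

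3. *The comparison of proportions is inferred, and the analysis plan is not shown.* Partly right. No test is assigned to each component, and a score analysis is neither stated nor excluded. But the cuts are stated rules and not omitted detail, and the natural test for a two-category variable here is this: "For individual outcomes, proportions will be compared using the chi-square test". BMI gives weight a continuous measure, but not one of the practices asked about.

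4. *The cut-offs may come from the validated scale.* They may. The recommendation column gives a BMI range and a sodium amount, not a number of answers, but Table 2 says that the assessment follows an adapted H-SCALE. Whether the cuts come from it cannot be checked here, so calling them arbitrary would go too far.

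5. *The power model is not the plan's test.* True. The plan names no cluster-level test. The model was used so that both versions of the outcome meet the same clustered comparison; the contrast between them is what counts.

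**Conclusion.** The point holds as a cheap improvement. The article's own rules reduce two multi-question counts in a primary outcome to yes/no and define no analysis of the counts. The direction of the loss is consistent across all cases run. Its size is conditional: about 4 to 12 power points at SMD 0.5 with 0.05 read as an ICC, about 1 to 4 at SMD 0.5 with little clustering, and about 10 to 23 at SMD 0.3 with an ICC of 0.0025 to 0.02. All figures assume 7 clinics per arm and 39 analysed per clinic.

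A reader might also take a move from 4 to 5 weight practices as a full success under this rule. The printed text does not support that, because 5 yes answers are coded nonadherent. Until the coding is reconciled, neither the percentage nor a mean score can be interpreted with confidence.

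**What to change.** In this order:

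1. Check the salt and weight rows of Table 2 against the questionnaire (Multimedia Appendix 1) and state for each item whether yes is the favourable answer. Correct the table or the scoring so that they agree.
2. In Table 2 and Data Analysis, make the primary comparison for these two components the between-arm difference in mean item score at 6 months (0–10 for weight management, 0–6 for salt, higher is better), with a 95% CI.
3. Report percent adherent at the existing cut-offs as a secondary result. Components asked with a single question (smoking, physical activity) stay binary.
4. If a power figure for these components is quoted, state the ICC and effect assumed and show a range.

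The cost is wording. The items are already collected with the same tool at baseline and at 6 months, so no new data or participants are needed. The downside is that a difference in mean score is less directly interpretable than a percentage, which is why the percentage is kept.
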